## Abstract

**Background:**

Seventy percent of women in Scotland have at least one baby, making pregnancy an opportunity to help most young women quit smoking before their own health is irreparably compromised. By quitting during pregnancy their infants will be protected from miscarriage and still birth as well as low birth weight, asthma, attention deficit disorder and adult cardiovascular disease. In the UK, the NICE guidelines: ‘How to stop smoking in pregnancy and following childbirth’ (June 2010) highlighted that little evidence exists in the literature to confirm the efficacy of financial incentives to help pregnant smokers to quit. Its first research recommendation was to determine: Within a UK context, are incentives an acceptable, effective and cost-effective way to help pregnant women who smoke to quit?

**Design and methods:**

This study is a phase II exploratory individually randomized controlled trial comparing standard care for pregnant smokers with standard care plus the additional offer of financial voucher incentives to engage with specialist cessation services and/or to quit smoking during pregnancy.

Participants (n = 600) will be pregnant smokers identified at maternity booking who, when contacted by specialist cessation services, agree to having their details passed to the NHS Smokefree Pregnancy Study Helpline to discuss the trial. The NHS Smokefree Pregnancy Study Helpline will be responsible for telephone consent and follow-up in late pregnancy. The primary outcome will be self reported smoking in late pregnancy verified by cotinine measurement. An economic evaluation will refine cost data collection and assess potential cost-effectiveness while qualitative research interviews with clients and health professionals will assess the level of acceptance of this form of incentive payment. The research questions are: What is the likely therapeutic efficacy? Are incentives potentially cost-effective? Is individual randomization an efficient trial design without introducing outcome bias? Can incentives be introduced in a way that is feasible and acceptable?

**Discussion:**

This phase II trial will establish a workable design to reduce the risks associated with a future definitive phase III multicenter randomized controlled trial and establish a framework to assess the costs and benefits of financial incentives to help pregnant smokers to quit.

**Trial registration:**

Current Controlled Trials ISRCTN87508788

## Background

Smoking during pregnancy increases miscarriage and stillbirth, accounting for up to 4000 UK deaths annually, and pre-term birth and low birth weight leading to perinatal morbidity [1]. A third of excess stillbirths and post-natal deaths associated with living in deprived areas are explained by smoking during pregnancy [2]. In Scotland 70% of women have a baby [3], making pregnancy an opportunity to help most women quit before their health is permanently compromised. In 2009, 24% of women booking for maternity care self-reported as current smokers [4]. Less than 1 in 20 of these women quit [5]. A study in the USA [6] in 2001 calculated the additional first year costs to health services as $1200 per smoker. Smoking is a major preventable cause of premature mortality for the mother, and lifelong benefits of quitting for children include reduced incidence of asthma and attention deficit disorder.

Following the 1998 White paper ‘Smoking Kills’, evidence-based National Health Service (NHS) smoking cessation services using behavioral support were developed [7-9] and now exist throughout Scotland [5]. Most of these services aim to provide tailored support (referred to in this paper as NHS Smokefree Pregnancy Services - NSPS) to pregnant women on a one-to-one basis, and evidence suggests that such interventions during pregnancy are effective [10]. Nicotine replacement therapy (NRT) is also offered, although its efficacy in pregnancy is not yet clear [10]. In Greater Glasgow & Clyde (GG&C), with 15,000 pregnancies per year, pregnant smokers identified at maternity booking are currently routinely referred to the NSPS on an ‘opt-out’ basis, without consent for transfer of contact information [7]. This practice is in keeping with the recent National Institute for health and Clinical Excellence (NICE) guidelines in the UK [11]. Women are then contacted by NSPS advisers who ask if they would like to quit and offer a face-to-face appointment in a clinic or home setting. If the client attends they set a quit date and a risk assessment for use of NRT during pregnancy is performed.

Participation figures for areas with recognized specialist smoking cessation in pregnancy services from a Scotland-wide audit are shown below [5]:

A. Estimated number of pregnant smokers at maternity booking [12], 8170 (100%).

B. Smokers identified by self report at routine booking questionnaire, 6128 (75%).

C. Smokers referred to specialist pregnancy cessation services, 3188 (39%).

D. Smokers engaged - face to face contact with specialist cessation service, 763 (10%)^a^.

E. Smokers who ‘set a quit date’, 779 (10%).

F. Smokers who had quit 4 weeks later, 236 (3%).

^a^Different denominator.

In Scotland, all women who book for maternity care are asked if they are current, former or never smokers (B above). At present 25% deny their habit (A to B) [12]. This problem is being addressed by routinely testing all pregnant women at maternity booking for carbon monoxide using a breath test [11]. Only half were referred (B to C) due to busy clinics and perceived client disapproval. Only 10% reached specialist cessation services such as those available in Glasgow (D). Nearly all of these ‘set a quit date’ (E) and 3 in 10 (F) quit. Some improvement (E to F) may be possible as 4 in 10 quit [13] with support from NHS cessation services in other parts of the UK.

Incentives are thought to increase participation and engagement [14,15], retention [16,17], and cessation [15-18]. If offered incentives, women who deny smoking may report as current smokers (A to B). Clients may self-refer or ask to be referred (B to C). With incentives, a greater proportion may engage (C to D) [5]. Improvement in the numbers quitting (D to F) will follow. In Scotland, when more pregnant smokers were referred, more engaged and more quit [5].

A 2009 Cochrane systematic review of interventions for promoting smoking cessation during pregnancy [10] asked: Do interventions improve quit rates? Are some interventions better than others? Figure 1 is a funnel plot describing the outcome from all included trials showing intervention better than control to the left. Fewer small trials on the right (control better than intervention) indicates some publication bias so the pooled risk ratio 0.94 may overestimate any combined positive effect. The four incentives trials showed significantly better outcomes than other interventions: pooled risk ratio 0.76 (95% confidence interval (CI) 0.71 to 0.91).

**Figure 1 F1:**
[figure not shown]
**Funnel plot.** Figure 1 is a funnel plot of all studies included in the Cochrane systematic review: interventions for promoting smoking cessation during pregnancy [10]. The overall risk ratio for smoking cessation in each study is plotted on the x axis. The sample size of each study is plotted on the y axis. The plot illustrates possible publication bias with a gap caused by ‘missing’ studies upsetting the symmetry on the right hand side of the figure, indicating that small negative studies may not have reached the point of publication. Diamond shaped symbols indicate individual randomization whereas square symbols indicate that cluster randomization was used in the trial. The four black diamond shapes on the left side represent the four incentives trials included in the review. The dashed vertical line crosses the x axis at the weighted mean risk ratio of smoking reduction in all studies comparing intervention with control – 0.94 (95 % confidence interval 0.93 to 0.95).

However, the incentives trials are all from the USA. The first trial was conducted 25 years ago and only included incentives as a minor part of an extensive intervention. Other incentives trials were small [16-18] and did not have a ‘no incentive’ control group [17,18]. None attempted to measure change in participation or engagement with an intervention. The NICE guidelines [11] issued in June 2010 highlighted that little evidence exists in the literature to confirm the efficacy of financial incentives to help pregnant smokers to quit. Its first research recommendation was: “Within a UK context, are incentives an acceptable, effective and cost-effective way to help pregnant women who smoke to quit?”

Since 2007, NHS Tayside in Scotland has piloted an incentives model - £12.50 per week of supermarket vouchers - to reward smoking cessation from quit date to 3 months after birth. The total payment for quitters is up to £650. The project has no formal contemporaneous control group but the number of women accessing cessation support has increased since incentives were introduced [19]. Women access the service at their local pharmacies, which provide NRT as well as support and validate whether the client has stopped smoking. This information initiates a payment onto a store card. During 2009, 169 (14%) of about 1200 pregnant smokers [5] joined the program (the equivalent of engagement) and 94 (8%) women had quit smoking 4 weeks later; 42 were still quit at delivery (personal communication, [name]). This cessation rate is higher than those obtained by other Scottish smoking cessation in pregnancy services, where the average quit rate at 4 weeks is 3%, and the best 5% [5]. A feasibility study for an incentives trial in Glasgow reported in January 2009 [20]. It explored how the Tayside program could be adapted for service configuration in Glasgow. The feasibility study provided the foundation for development of this trial.

This phase II trial will provide the tools required to run a future appropriately powered definitive phase III multicenter randomized controlled trial. The aim of that future phase III trial will be to establish whether or not incentives increase engagement with services, quit attempts and successful cessation to provide a more cost-effective pregnancy smoking cessation service model generalizable to the whole UK and beyond.

## Design and methodology

### Population

In 2010 there were 58,051 births in Scotland with 14,155 (24%) to mothers resident in NHS GG&C Health Board area. Twenty-six percent of births in Scotland are to women who live in the most deprived quintile, whereas in GG&C it is 44% [21]. Of the most deprived women who were asked, 35% self reported that they smoked at maternity booking compared with 7.1% of the least deprived [22]. Overall, in GG&C 25% of women self report as current smokers at maternity booking.

### Design

The study is designed as a phase II single blinded (outcome assessor blind to randomization status at follow-up telephone contact) individually randomized controlled trial. The procedures are illustrated schematically in Figure 2 and detailed in the text.

**Figure 2 F2:**
[figure not shown]
**Flow diagram for Cessation in Pregnancy Incentives Trial (CPIT).** Figure 2 projects the flow of pregnant women through the trial over a 12-month period. In the NHS Greater Glasgow & Clyde study area, 15,000 pregnancies are recorded at maternity booking; 5,000 are to smokers, some who conceal their habit, and 3,000 are identified at maternity booking by self-report as current smokers. Their information is routinely passed to NHS Smokefree Pregnancy Services (NSPS) using an automated system. Attempt is made to contact all self reported smokers. We estimate that 500 will not be contactable by NSPS and that 500 will decline permission for their details to be passed to the NHS Smokefree Pregnancy Study Helpline (Study Helpline). Once details have been passed, 500 will not be contactable leaving 1,500 contacted by the Study Helpline. We expect that 600 to 900 will decline consent leaving 600 to 900 who agree to enroll in the study over 12 months. Of these, 300 will be randomly allocated to the intervention group to be offered incentive payments as well as standard care to stop smoking during pregnancy and 300 will be randomly allocated to receive the offer of standard care without incentive payments to quit smoking.

### Research questions

#### *Trial*

1. What is the likely therapeutic efficacy of financial incentives to encourage women to attend specialist cessation services, to set a quit date, to quit smoking and be abstinent at 34 to 38 weeks gestation towards the end of pregnancy?

2. Is individual randomization an efficient trial design without compromising validity through bias due to differential follow-up of disaffected control arm participants?

#### *Health economic study*

3. Are incentives potentially a cost-effective means of helping pregnant women to stop smoking?

#### *Qualitative study*

4. Can incentives be introduced in a way that is feasible and acceptable to women and service providers and are there any unintended consequences?

### NHS Smokefree Pregnancy Services Greater Glasgow & Clyde Health Board area

At their maternity booking appointment pregnant women in NHS GG&C are asked for consent for screening which includes procedures to identify and offer treatment to current smokers – self report and routine carbon monoxide breath test with follow-up by NSPS. All women with either a carbon monoxide level of 5 ppm and above or self reported as current smokers (at least 1 cigarette in the last week) are notified to NSPS using a rapid electronic system. NSPS advisers contact these women by telephone and offer a smoking cessation counseling service which utilizes ‘Withdrawal Oriented Therapy’ [23]. Support includes a face-to-face appointment, weekly telephone support for 4 weeks and the offer of NRT dispensed by local pharmacies free of charge to support a quit attempt for up to 12 weeks.

### Trial inclusion criteria

Participants must satisfy the following criteria to be included in the study:

· age at least 16 years and pregnant less than 24 weeks gestation at maternity booking.

· self report as current smokers.

· have a carbon monoxide breath test result of 7 ppm or greater - NICE guideline level for referral of pregnant smokers – PH26 [11].

· live in the NHS GG&C Health Board area.

· give permission for their contact details to be passed to NHS Smokefree Pregnancy Study Helpline.

· be able to understand and speak English in order to provide verbal telephone consent to take part in the trial.

### Screening

Early in the first telephone contact call from an NSPS adviser, eligible smokers will be given information about the trial and asked to give their verbal permission for contact details to be passed to the NHS Smokefree Pregnancy Study Helpline so that formal trial telephone consent procedures can take place. The Caldicott Guardian has approved this verbal permission required to pass this contact information. Those who give permission for contact details to be passed will be sent a letter and a trial information sheet outlining the nature and importance of the trial. The NSPS adviser will then continue with standard treatment and follow-up procedures.

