### Consent and randomization procedure

At least 7 days after the first NSPS contact call, eligible smokers who allow their contact details to be passed on will be contacted by the Helpline to undergo formal consent procedures. Telephone contact will be attempted on three occasions at the time slot preferred by the client - weekday, evening or weekend - after which no further attempts at enrollment will be made. During the consent call potential participants will be fully informed about the nature and relevance of the trial, and exactly what will be involved if they agree to take part. Early in the consent call potential participants will be asked to provide information not asked for at maternity booking including questions measuring level of addiction to nicotine and partner smoking habits. Audio recordings of the consent process will be stored in accordance with Good Clinical Practice guidelines. Eligible smokers who consent to take part in the trial will be sent a written copy of their consent form. Individuals who give informed consent will be enrolled in the trial and randomized. The random allocation will be fed back to the participant. The Helpline adviser cannot influence or predict the random allocation which is integrated into the clinical information system. It will also provide a concealed (not available to the NHS Smokefree Pregnancy Study Helpline adviser during the consent call) random date between 34 and 38 weeks gestation for this pregnancy when the Helpline will contact the participant again to ascertain the primary outcome measure of self reported smoking during the last 8 weeks which will be corroborated by cotinine measurement.

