#### *Eligibility criteria*

Self reported smoking status at maternity booking, carbon monoxide breath test level at maternity booking, date of carbon monoxide reading, age at first telephone contact, English speaking, gestation at booking, consent, copy of consent form sent.

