#### *Smoking addiction level and other*

Fagerstrom questions [24] score out of 10, parity, partner smokes.

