#### *Secondary outcomes*

Engagement with specialist pregnancy cessation services is achieved if the participant arrives at a first face-to-face appointment with the NSPS adviser and sets a quit date.

Quit at 4 weeks after quit date will be ascertained with the question ‘Have you smoked in the last 2 weeks, even a puff?’ at routine telephone contact by the NSPS adviser. This will be corroborated by a carbon monoxide breath test collected at routine pharmacy visits to collect NRT. These data will be available from both intervention and control groups.

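### Standard cessation care starts at least 7 days before randomization and engagement is not tied to allocation, so appointments attended beforehand count in both arms and dilute the engagement comparison

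*Protocol article*

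**What the plan says.** All references are to the Protocol article.

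- **Care before consent.** Under Screening, the adviser raises the trial early in the first call, asks permission to pass on contact details, and then: "The NSPS adviser will then continue with standard treatment and follow-up procedures". The section on NHS Smokefree Pregnancy Services (NSPS) describes that care: "Support includes a face-to-face appointment, weekly telephone support for 4 weeks and the offer of NRT dispensed by local pharmacies". The Background adds that a woman who attends sets a quit date.
- **Randomization later.** The section on the consent and randomization procedure sets the timing of the Helpline call: "At least 7 days after the first NSPS contact call, eligible smokers who allow their contact details to be passed on will be contacted". Up to three contact attempts are allowed and no maximum delay is given. Allocation is disclosed towards the end of the same call.
- **Baseline data.** The eligibility items include "Self reported smoking status at maternity booking, carbon monoxide breath test level at maternity booking, date of carbon monoxide reading". The other items are "Fagerstrom questions [24] score out of 10, parity, partner smokes". Neither list includes prior attendance, an existing quit date, or smoking status on the day of randomization.
- **Outcome.** Under Secondary outcomes, engagement "is achieved if the participant arrives at a first face-to-face appointment with the NSPS adviser and sets a quit date". No start date for counting is given.
- **First payment.** Under Voucher incentive payments, the first £50 is tied to that same event. The text does not say whether attendance before allocation qualifies.

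**The concern.** Usual care can produce the engagement event while the woman is still waiting for her consent call. She may attend and set a quit date in that interval, and then be randomized. As written, she meets the engagement definition in whichever arm she enters, and an offer made afterwards cannot change that.

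Such events are balanced between arms in expectation. They add about the same number to each side and pull the engagement ratio towards 1. This matters because research question 1 starts with attendance and setting a quit date, and because the Background says the future phase III trial will ask whether incentives raise engagement, quit attempts and cessation. A control-arm engagement rate and effect estimate that include events before allocation would be carried into its planning.

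The interval is not idle. Women receive a letter and information sheet about the trial during it, and the Recruitment section expects knowledge of the trial to lead more smokers to consider quitting.

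**Working it through.** **1. The plan's own power figure.** Inputs from Sample size and Figure 2: 300 per arm, 4% in usual care, 5% level (two-sided assumed), continuity-corrected test. With d = p2 − p1 and p̄ the mean of the two rates,

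power = Φ{ [d − 1/n − 1.96·√(2p̄(1−p̄)/n)] / √[(p1(1−p1) + p2(1−p2))/n] }.

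- 4% v 11.4%: 90.3% (stated 90%).
- 4% v 10.2%: (0.062 − 0.0033 − 0.0411)/0.0208 = 0.84, so 80.1% (stated 80%).

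Both figures reproduce and are not in dispute.

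**2. Engagement.** Let f be the share of control-arm engagement that happens before allocation, and suppose the offer multiplies later engagement by 1.5. Both f and 1.5 are assumptions. Then

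observed ratio = f + 1.5·(1 − f).

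- f = 0.25: 0.25 + 1.125 = 1.375, or 1.38.
- f = 0.50: 0.50 + 0.75 = 1.25.

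The ratio does not depend on the overall engagement rate. For a sense of scale, the audit in the Background gives 763/3188 = 24% of referred smokers engaging. This is crude, because the article's footnote flags a different denominator. At 24%, f = 0.25 to 0.50 means 6% to 12% of each arm has the outcome before allocation:

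| f | All randomized, all events | Ratio | Not engaged at allocation, later events | Ratio |
|---|---|---|---|---|
| 0.25 | 24% v 33% | 1.38 | 0.18/0.94 = 19.1% v 0.27/0.94 = 28.7% | 1.5 |
| 0.50 | 24% v 30% | 1.25 | 0.12/0.88 = 13.6% v 0.18/0.88 = 20.5% | 1.5 |

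The restricted set recovers the assumed effect and keeps 282 or 264 of 300 women per arm (300 × 0.94 and 300 × 0.88). On the difference scale the loss is smaller: 9.0 instead of 9.6 points, or 6.0 instead of 6.8.

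**3. Late-pregnancy quitting.** Suppose 1%, 2% or 3% of each arm has already stopped at randomization, stays stopped, and comes on top of the planned 4% v 10.2%. All three conditions are assumptions.

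| Already stopped | Rates | Risk ratio | Power |
|---|---|---|---|
| 0% | 4% v 10.2% | 2.55 | 80% |
| 1% | 5% v 11.2% | 2.24 | 75% |
| 2% | 6% v 12.2% | 2.03 | 71% |
| 3% | 7% v 13.2% | 1.89 | 67% |

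In the Tayside figures in the Background, 42 of 94 four-week quitters (45%) were still abstinent at delivery. Applying that retention, the additions become 0.45, 0.89 and 1.34 points, the risk ratio 2.39, 2.27 and 2.16, and power 78%, 76% and 74%. The difference is 6.2 points throughout.

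**The case against.** A reader might infer that every comparison in the trial is diluted, and that power for the primary outcome falls to 67%. The article does not support that.

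- **Follow-up.** The Primary outcome section names the proportion followed up in each arm as the important aspect for this phase II trial. Early attendance or quitting does not dilute that comparison.
- **Late-pregnancy quitting.** This is abstinence over the last 8 weeks, asked at 34 to 38 weeks in women who booked before 24 weeks. The window will ordinarily fall after allocation. A woman who stopped early must still remain abstinent, and the 4-week, 12-week and final payments can still influence her. The 1% to 3% has no source in the article, and the assumed 4% may already include early quitters.
- **Four-week quitting.** This is assessed 4 weeks after the quit date, so it precedes allocation only if the quit date fell about 4 weeks before the consent call.
- **Smoking status.** It would be too strong to say that nothing about smoking is asked. The Fagerstrom questions come before randomization, and the consent section introduces its items as examples. They are not stated to be a status check, however, and they cannot show attendance or a quit date.
- **Counting rules.** These may sit in an analysis plan that is not shown, and service appointment dates may allow engagement to be classified later. That is fair for engagement. But if smoking status on the day of randomization is not asked, no analysis plan can recover it.
- **Purpose.** The trial is stated not to be designed to detect a specified difference. That lowers the weight of the power figures. It does not remove the problem for estimates meant to inform phase III.

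**Conclusion.** The point holds for engagement. Care that can produce the outcome starts before allocation, prior attendance is not among the listed baseline items, and the definition does not require the event to follow randomization. Followed as written, the plan counts appointments that the offer cannot have influenced and shrinks the engagement ratio: 1.5 would be seen as 1.38 to 1.25 if 25% to 50% of control-arm engagement came early. Those shares are assumptions. The article gives no figure for engagement before allocation, so the real loss may be smaller or larger.

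For the 4-week and late-pregnancy quit outcomes the effect is partial and its size cannot be derived. The follow-up comparison is untouched. A reader might also infer bias between arms, but events before allocation are balanced in expectation, so the cost is lost contrast, not confounding.

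Separately, the Screening, Consent and randomization procedure, Voucher incentive payments and Secondary outcomes sections leave open whether attendance before allocation triggers the first voucher, and must be reconciled.

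**What to change.** 1. In the existing consent call, before randomization and beside the addiction questions, record whether the woman currently smokes, and whether she has already attended NSPS or set a quit date.
2. Define the engagement outcome as a first appointment plus quit date after randomization. Analyse it in women not engaged at randomization, with the same rule in both arms, and report engagement before allocation by arm.
3. Classify women already enrolled from NSPS appointment dates. On 9 June 2012 there were 199 of 600 enrolled, so the new questions could cover up to 401.
4. Keep the intention-to-treat analysis of the primary outcome in all randomized women. Add a sensitivity analysis by smoking status at randomization where it was recorded.
5. Do not add a current-smoking eligibility rule now; it would change the population part-way through recruitment.
6. Reconcile the four sections named above on the first voucher.

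The cost is two extra questions, a small amendment and a slightly smaller engagement analysis set.
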